### Sample size

We use 90% power and 0.05 significance level to test a 15 ml difference in FEV_1_ growth per year between Central ULEZ and Luton comparison cohorts. For 40 schools/arm with 40 children from any of school years 2, 3, or 4, the study is powered for 15ml per year difference in FEV_1_ growth between the comparison zone and ULEZ. The total target sample size is therefore 3,200 children, comprising 1,600 in the London cohort and 1,600 in the Luton cohort.

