### Data

#### Statistical methods

The primary outcome variable of post bronchodilator FEV_1_, and secondary outcome variables of air pollution, post bronchodilator FVC and physical activity will be analysed longitudinally through a mixed effect model. The model assesses the interaction effect of time and study group to determine the difference in variable change between the intervention group (London) and comparison group (Luton). Mixed effects models using a random intercept term are robust to the biases of missing data and the clustering effect of recruiting participants from multiple schools, facilitating a longitudinal design in a highly transient population. Primary and secondary outcome variables will be adjusted to account for known covariates of gender, asthma diagnosis, ethnicity, deprivation, [38] age, height, and BMI. Secondary covariates which may be included after sensitivity analysis include socioeconomic status, stress, and physical activity. For linking air pollution data with lung function over time, a more complex mixed effect model with three levels will be used, the levels being child, school, and group. These will be tested first on a complete model with all levels, if models are not identifiable, then simpler models will be tried with fewer levels. These models would allow for the effects of each air pollutant to be tested against lung function at each level as well as over time.

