## Discussion

Air pollution is the regarded as the largest single environmental risk to health, with seven million deaths globally attributed annually [39]. Environmental health and sustainable development goals identified by the WHO highlight the need for effective preventative interventions to protect children from adverse environmental exposures including air pollution [3]. In the UK, road traffic represents the largest contributor to air pollution in urban areas, [40] with the period between 1949 and 2012 seeing a tenfold increase in the distance travelled by the average person in their car [2]. There is an urgent need to identify and quantify the impacts of effective air quality improvement health policy interventions. Such interventions are often costly to implement requiring large alterations in social functioning and urban infrastructure. It is essential therefore that evaluations deliver robust evidence to justify their implementation.

The use of a parallel prospective cohort design enables the CHILL study to deliver the most reliable conclusions to date on exposure-response functions and causal relationships between pollutant exposures and children’s health and lung development. To our knowledge, no previous study has prospectively evaluated a major city-wide air quality mitigation strategy using this design. Like many current research studies, the COVID-19 pandemic has created both operational difficulties in delivering studies, and scientific challenges in disentangling effects of planned interventions from those caused directly from COVID-19 infection and indirectly from attempts to mitigate effects of the pandemic on society. In response to the COVID-19 pandemic, two amendments are made within the study. Firstly, a fifth year of data collection is added to make up for the inability to capture outcome data during school closures and COVID-19 lockdowns. Secondly, where possible the children moving up into secondary school are followed up with a health assessment and collection of the parental questionnaire. By extending data collection by a further year, following children up as they move to secondary schools, collecting evidence of SARS-CoV-2 infection in participants, and collecting contextual data of local impacts of lockdowns, we hope to draw robust conclusions on the effects of implementing the ULEZ on children’s health and development.

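### The pollutant–lung function model makes study group a level, but two groups cannot support a group variance or a group-level pollutant effect separable from other London–Luton differences

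*Protocol article*

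**What the plan says.** The Statistical methods section of the protocol article describes two models.

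- The first, for post-bronchodilator FEV1 and several secondary outcomes, is a mixed model with a random intercept. Group enters as a comparison over time: "The model assesses the interaction effect of time and study group".
- The second links pollution to lung function. Here "a more complex mixed effect model with three levels will be used, the levels being child, school, and group". All levels are tried first; "if models are not identifiable, then simpler models will be tried with fewer levels". The stated purpose is that these models would "allow for the effects of each air pollutant to be tested against lung function at each level as well as over time".

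The study has one intervention area and one comparator (Study design; Study population and setting). The Sample size section plans on many more units below group: "For 40 schools/arm with 40 children from any of school years 2, 3, or 4". The Air pollution modelling section gives exposure at residential address, so it differs between children as well as over time.

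**The concern.** A level in a mixed model is normally a population of units whose variance is estimated. Schools and children qualify; two study areas do not. The same section already treats group as a fixed comparison in the first model, so the two descriptions do not fit together.

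The larger difficulty is the stated intention to test each pollutant at each level. At group level there are two units, and they differ in much besides pollution. A coefficient from that level could be reported as an exposure-response estimate when it only restates the London–Luton comparison in pollutant units. The analysis is not peripheral: the Abstract words the primary outcome as the effect of changes in pollutant exposure on lung function growth, and the Discussion claims reliable conclusions on exposure-response functions.

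A smaller issue is the fallback. It says that levels may be removed but not that the child level must stay.

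**Working it through.** No figure in the protocol can be reproduced for this point. The documents supply the two groups, 40 schools per arm, 40 children per school, the school ICC of 0.001 (Assumptions) and up to five annual visits (Table 1). Other variance components are assumed.

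**1. Group variance on 1 df.** A mean square on d degrees of freedom gives 95% limits for the standard deviation of √(d/χ²(0.975)) to √(d/χ²(0.025)) times the estimate.
- Two groups, d = 1: quantiles 5.02 and 0.00098, so 0.45 to 31.9 times.
- For comparison, 80 units (the number of schools), d = 79: 0.87 to 1.18 times.

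These limits describe a mean square. A variance component can also be estimated at zero, so that was checked directly. Assume total variance 1: school 0.001, child 0.8, residual 0.199, four visits, balanced data. The variance of a group mean, apart from the group effect, is v = (0.001 + 0.8/40 + 0.199/160)/40 = 0.000556. The balanced estimate is zero when an F variable on 1 and 78 df falls below 1/(1 + σ²/v), where σ² is the true group variance.

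| True group variance | Chance of a zero estimate |
|---|---|
| 0 | 68% |
| 0.001 | 45% |
| 0.005 | 25% |
| 0.01 | 18% |
| 0.05 | 8% |

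A simulation of 20,000 runs agrees. At a true value of 0.01, 95% of its estimates lie between 0 and about 0.05, up to five times the truth.

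**2. Pollutant effect at group level.** With two group means of growth and two of pollutant change, the slope is (London growth − Luton growth) / (London pollutant change − Luton pollutant change). Two points less two parameters leave 2 − 2 = 0 residual df. Yearly means give up to five London–Luton differences instead of one, but the number of groups is still two. Anything else that moves differently in the two places over those years fits the same series.

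**3. If the child level were dropped.** For exposure constant within child, reported SE / true SE = 1/√(1 + (T − 1)ρ), with T visits and within-child correlation ρ (assumed).

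| T | ρ = 0.5 | ρ = 0.8 | ρ = 0.9 |
|---|---|---|---|
| 3 | 0.71 | 0.62 | 0.60 |
| 4 | 0.63 | 0.54 | 0.52 |
| 5 | 0.58 | 0.49 | 0.47 |

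True type I error at nominal 5% runs from 17% (T = 3, ρ = 0.5) to 36% (T = 5, ρ = 0.9).

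If a share w of exposure variance is within child, the factor becomes (1 + (T − 1)ρ)·B + (1 − ρ)·W, with B = (1 − w) + w/T and W = w(T − 1)/T. For T = 4 and ρ = 0.8:
- w = 0.3: 3.4 × 0.775 + 0.2 × 0.225 = 2.68; SE ratio 0.61; type I error 23%.
- w = 0.6: 3.4 × 0.55 + 0.2 × 0.45 = 1.96; SE ratio 0.71; type I error 16%.

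Simulation with 400 runs per setting gave 21% to 24% and 12% to 16% respectively; the lower values come from runs that also had random child slopes. For purely within-child change the factor is 1 − ρ = 0.2, so the reported SE would be too large (1/√0.2 = 2.2 times), not too small.

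**4. If the school level were dropped.** For a school-level exposure with one reading per child, the design effect is 1 + 39 × 0.001 = 1.039. The SE ratio is 1/√1.039 = 0.98 and type I error is about 5.5%.

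**The case against.** The strongest reply is that the weak component is group itself. If the full model fails, dropping group is the natural step and does no harm. The child level is supported by repeated readings on a target of 3,200 children and has no identifiability problem, and nothing in the text points to removing it. This stands. A reader might infer that the plan will produce invalid standard errors by losing the child or school level. The documents do not support that: loss of the child level is only a possibility left open by the wording, and loss of the school level costs about 2% of the SE at the protocol's own ICC. That ICC is for FEV1 rather than its growth, but no other value is given.

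A reader might also infer that the full model is bound to be singular. It is not: the chance of a zero estimate falls from 68% to 18% as the true group variance rises from zero to 1% of the total. Nor does the text say outright that group is random. If it is meant as a fixed effect, the variance problem disappears, but a pollutant effect tested at group level is still confounded with place.

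The words about testing over time mean that the group-level effect need not equal a single London–Luton contrast. That is fair, but yearly means add time points, not groups.

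Finally, the order in which a model is simplified and the handling of children who move to secondary school are commonly left to an analysis plan. Their absence from a condensed article is not counted here.

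**Conclusion.** The point holds in a limited form. The article states that group is a level and that pollutant effects will be tested at each level. With two groups, a random group variance is likely to be estimated at zero or very imprecisely, and a group-level pollutant effect cannot be told apart from any other London–Luton difference. The lack of separation follows from the count of groups and needs no assumption. The zero-estimate percentages rest on the assumed variance components and balanced data.

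The standard-error range of about 0.5 to 0.7 is conditional: it applies only if the child level were removed, and only to exposure that differs between children. It supports a one-sentence safeguard, not a claim that the analysis is invalid. The primary time-by-group comparison of FEV1 growth is not affected, so this is a worthwhile correction to the exposure-response model and not a threat to the main comparison.

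**What to change.** Reword the second model in Statistical methods:

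- Structure: visits within children within school of enrolment, with group and group × time as fixed effects.
- Exposure: split each pollutant into within-child change and between-child mean, so that the exposure-response estimate does not depend on the contrast between the two areas.
- Interpretation: drop the group-level pollutant test, or state that any such quantity is not an exposure-response estimate.
- Fallback: state that the child level is always kept if the model must be simplified. The detailed order can go in the analysis plan.

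The cost is a change of wording, with no extra data or participants. The one loss is that no group-level pollutant test is reported. The primary analysis stays as written.

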#### Sensitivity analyses and missing data

Sensitivity analyses will be conducted to ensure no bias in the primary results due to missing data by contrasting an “all children” data set to a “complete history” data set. Temporal individual and school exposure assessments will be contrasted to the rest of the cohort to assess for cluster bias such as rebound lung growth and high non-traffic related air pollution change unrelated to the ULEZ.

Z-scores will be calculated for each continuous variable and will be examined for values > 4. Plots of residuals will be inspected for suspected outliers. Should any be found, raw data will be checked for accuracy. If the data are found to be correct, a model will be fitted excluding outliers as a sensitivity analysis to assess impact on the primary data set.

#### Additional analyses

Secondary analysis will assess the effect of the intervention on participants by quintile of deprivation, ethnic group and sex. Specifically, assessment will examine the following outcomes: change in air quality for each individual pollutant; lung growth; change in generic quality of life; change in respiratory symptoms; change in respiratory infection rates; change in health care use and change to small-area socioeconomic, population and mortality outcomes.

### Assessment of cost-effectiveness

An economic evaluation will relate costs associated with introducing the ULEZ to the impact of air pollution on children’s lung growth, school attendance, parent work productivity and use/costs of healthcare services and quality of life. Analysis will use a cost-consequences approach, as recommended in NICE (National Institute of Health and Care Excellence) public health guidance.

Downloads of each child’s electronic health record will provide data on primary and secondary care use, while unit costs from national sources will be applied to all resource use to estimate individual-level costs. Impacts of school absence will be assessed in relation to meeting government attendance targets and consequent lost productivity/income due to work absence by parents, using appropriate assumptions, national wage rate data and a human capital approach to costing. Quality of life and quality-adjusted life years will be assessed by administering the parent completed proxy Child Health Utility 9D and its associated general population-based preference weights. The cost-consequences analysis will report means and standard deviations for all costs and outcomes for both cohorts that will be assessed using a mixed effects model to assess interaction effects of time and study site.

### Ethics, safety and dissemination

The study is approved by Queen Mary University of London Research Ethics Committee (reference 2018/08), and NHS Research Ethics Committee (reference 22/WS/0065). The Chief Investigator has the overall oversight, responsibility and a duty to ensure that safety monitoring and reporting is conducted in accordance with the sponsor’s requirements and that an annual progress report, including any safety issues, is submitted yearly to the main research ethics committee and the sponsor. Six monthly progress reports are sent to the funder.

### Governance

An Independent Scientific Committee (ISC) comprising a chair, five scientific members and two PPI members monitors the study on behalf of the funder and sponsor. The ISC meets with the CI and study team at least annually.

### Data monitoring and auditing

Monitoring and auditing of data is carried out by the PCTU Quality Assurance team.

### Dissemination plan and project outputs

The CHILL study will disseminate study progress, maximising public and professional awareness of the study and its relevance to public and child health. We expect to reach the following groups:

study participants, their families, schools and local study communities;the public - including voluntary organisations, charities, lay and pressure groups.government - including parliament, national, regional, local councils, International governments;academia – including universities, NIHR, Royal Colleges, National Institute for Health and Care Excellence (NICE), World Health Organization (WHO), and leading international research groups;industry – vehicle and transport-related manufacturers.

The outputs needed to target these audiences vary (Additional File 4 - Fig. 4).

## Discussion

Air pollution is the regarded as the largest single environmental risk to health, with seven million deaths globally attributed annually [39]. Environmental health and sustainable development goals identified by the WHO highlight the need for effective preventative interventions to protect children from adverse environmental exposures including air pollution [3]. In the UK, road traffic represents the largest contributor to air pollution in urban areas, [40] with the period between 1949 and 2012 seeing a tenfold increase in the distance travelled by the average person in their car [2]. There is an urgent need to identify and quantify the impacts of effective air quality improvement health policy interventions. Such interventions are often costly to implement requiring large alterations in social functioning and urban infrastructure. It is essential therefore that evaluations deliver robust evidence to justify their implementation.

The use of a parallel prospective cohort design enables the CHILL study to deliver the most reliable conclusions to date on exposure-response functions and causal relationships between pollutant exposures and children’s health and lung development. To our knowledge, no previous study has prospectively evaluated a major city-wide air quality mitigation strategy using this design. Like many current research studies, the COVID-19 pandemic has created both operational difficulties in delivering studies, and scientific challenges in disentangling effects of planned interventions from those caused directly from COVID-19 infection and indirectly from attempts to mitigate effects of the pandemic on society. In response to the COVID-19 pandemic, two amendments are made within the study. Firstly, a fifth year of data collection is added to make up for the inability to capture outcome data during school closures and COVID-19 lockdowns. Secondly, where possible the children moving up into secondary school are followed up with a health assessment and collection of the parental questionnaire. By extending data collection by a further year, following children up as they move to secondary schools, collecting evidence of SARS-CoV-2 infection in participants, and collecting contextual data of local impacts of lockdowns, we hope to draw robust conclusions on the effects of implementing the ULEZ on children’s health and development.

With increasing proportions of the world’s population now living in large urban areas commonly far exceeding WHO pollution limit guideline, [3] CHILL study findings will have important implications for the design and implementation of LEZs and Clean Air Zones in the UK, Europe and beyond.

## Data Availability

The datasets used and/or analysed during the current study are available from the corresponding author upon reasonable request.

## Abbreviations

ARC: Applied Research Collaboration
AURN: Automatic Urban & Rural Network
BMI: Body mass index
CHILL: Children’s Health in London and Luton
CHS: California Children’s Health Study
CHU9D: Child Health Utility 9 Dimensions questionnaire
CLAHRC: Collaboration for Leadership in Applied Health Research and Care
CMAQ: Community Multiscale Air Quality Modelling System
COVID-19: SARS-CoV-2 Coronavirus
FEV_1_: Forced Expiratory Flow in one second
FVC: Forced Vital Capacity
GPS: Global Positioning Satellite
GP: General Practitioner
HDV: Heavy duty vehicles
HES: Hospital Episode Statistics
HPRU: Health Research Health Protection Research Unit
ICC: Intra-class correlation
ISAAC: International Study of Asthma and Allergy
ISC: Independent Steering Committee
LAQN: London Air Quality Network
LEZ: Low Emission Zone
NHS: National Health Service
NICE: National Institute of Health and Care Excellence
NIHR: National Institute for Health Research
NOx: Nitrogen oxides
NO_2_: Nitrogen dioxide
O_3_: Ozone
PCTU: Pragmatic Clinical Trials Unit
PHE: Public Health England
POA: Primary Organic Aerosol
PM_2.5_: Particulate matter with a diameter of less than 2.5micrograms
PM_10_: Particulate matter with a diameter of less than 10 micrograms
PPI: Patient and public involvement
PMG: Project Management Group
QMUL: Queen Mary University of London
QR: Quick Response code
SOA: Secondary Organic Aerosol
ULEZ: Ultra Low Emission Zone
UKHSA: UK Health Security Agency
WRF: Weather Research and Forecasting model
WHO: World Health Organization
